# The CErebro Placental RAtio as indicator for delivery following perception of reduced fetal movements, protocol for an international cluster randomised clinical trial; the CEPRA study

**DOI:** 10.1186/s12884-021-03760-2

**Published:** 2021-04-09

**Keywords:** Reduced fetal movements, Decreased fetal movements, Cerebroplacental ratio, CPR, Placental insufficiency, Stillbirth, Fetal hypoxia, Neonatal morbidity

## Abstract

**Background:**

Routine assessment in (near) term pregnancy is often inaccurate for the identification of fetuses who are mild to moderately compromised due to placental insufficiency and are at risk of adverse outcomes, especially when fetal size is seemingly within normal range for gestational age. Although biometric measurements and cardiotocography are frequently used, it is known that these techniques have low sensitivity and specificity. In clinical practice this diagnostic uncertainty results in considerable ‘over treatment’ of women with healthy fetuses whilst truly compromised fetuses remain unidentified. The CPR is the ratio of the umbilical artery pulsatility index over the middle cerebral artery pulsatility index. A low CPR reflects fetal redistribution and is thought to be indicative of placental insufficiency independent of actual fetal size, and a marker of adverse outcomes. Its utility as an indicator for delivery in women with reduced fetal movements (RFM) is unknown. The aim of this study is to assess whether expedited delivery of women with RFM identified as high risk on the basis of a low CPR improves neonatal outcomes. Secondary aims include childhood outcomes, maternal obstetric outcomes, and the predictive value of biomarkers for adverse outcomes.

**Methods:**

International multicentre cluster randomised trial of women with singleton pregnancies with RFM at term, randomised to either an open or concealed arm. Only women with an estimated fetal weight ≥ 10th centile, a fetus in cephalic presentation and normal cardiotocograph are eligible and after informed consent the CPR will be measured. Expedited delivery is recommended in women with a low CPR in the open arm. Women in the concealed arm will not have their CPR results revealed and will receive routine clinical care. The intended sample size based on the primary outcome is 2160 patients. The primary outcome is a composite of: stillbirth, neonatal mortality, Apgar score < 7 at 5 min, cord pH < 7.10, emergency delivery for fetal distress, and severe neonatal morbidity.

**Discussion:**

The CEPRA trial will identify whether the CPR is a good indicator for delivery in women with perceived reduced fetal movements.

**Trial registration:**

Dutch trial registry (NTR), trial NL7557. Registered 25 February 2019.

## Background

Maternal perception of reduced fetal movements (RFM) occurs in approximately 6 to 15% of pregnancies [1]. RFM often results from relatively benign causes such as an altered fetal position or maternal distraction due to other activities or stress. In some cases, however, it is an important indicator pointing towards placental insufficiency. Placental insufficiency is usually a chronic process of impaired exchange at the maternal-fetal interface, leading to a deprived nutritional status of the fetus, until acute hypoxia becomes life threatening. If long-lasting and/or severe, fetuses typically become small for gestational age. If the onset of placental insufficiency occurs in late gestation, fetal size is more likely to be within the normal range and the chronic placental dysfunction remains undetected. In these cases, RFM may be the first sign of placental insufficiency and acute fetal compromise [2].

RFM is associated with a 2.4–5-fold increase in stillbirth and other adverse outcomes such as asphyxia, neurodevelopmental impairment in the offspring and maternal hypertensive disease [3, 4]. Although the stillbirth rate (> 28 weeks gestation) in the Netherlands has declined to 2.3 per 1000 in 2015, a large proportion of stillbirths remains unexplained and in 20–30% of cases substandard care is identified. Among these substandard care factors, failure to respond to RFM is important. There is still a large difference in stillbirth rates between high-income countries, varying between 1.4 and 3.7 per 1000 pregnancies from 28 weeks gestational age onwards [5]. Although these rates are declining, there is considerable variation between countries. This variation indicates ample room for improvement.

Stillbirth prediction is difficult and the fear of vital consequences leads to substantial overtreatment of women reporting RFM. Functional parameters, such as Doppler ultrasound and serum biomarkers, can help distinguish the compromised fetuses from healthy fetuses. A low cerebroplacental ratio (CPR) on Doppler ultrasound reflects a decrease in resistance in the middle cerebral artery (cerebral flow) and/or an increased resistance in the umbilical artery (placental flow) indicating redistribution of the fetal circulation: a compensatory adaptation to nutrient and oxygen deprivation due to placental insufficiency. A low CPR can identify a compromised fetus regardless of fetal size [6–9], and using the CPR combined with RFM may aid prediction and consequently prevention of stillbirth [10].

The incidence of an abnormal CPR in RFM is approximately 6% [4]. There are no studies of a management strategy based on an abnormal CPR for RFM. In a systematic review that included pregnancies of any risk profile, the CPR outperformed the umbilical artery pulsatility index in the prediction of emergency delivery for fetal distress and prediction of composite adverse outcome. A pooled sensitivity of 0.93 and specificity of 0.74 for perinatal death and a sensitivity of 0.59 and specificity of 0.91 for a composite adverse outcome was found for a CPR <5th centile (equivalent to CPR < 1.1), independent of birth weight [7, 11]. When analysing individual patient data from studies included in this systematic review, the CPR showed no added predictive value for adverse perinatal outcome beyond the umbilical artery pulsatility index, irrespective of gestational age or fetal size [12]. A possible explanation for this controversy could be that in the latter continuous data were used whereas in the review a cut off value was applied to determine (ab)normality.

It is unclear whether planned delivery for women presenting with RFM based on CPR achieves better outcomes than expectant management. Clinicians need to balance the risks of prolonged placental insufficiency associated with a higher risk of adverse outcomes including death against the risks of immediate delivery [9]. This uncertainty translates into considerable practice variation regarding the use of CPR for management of women reporting RFM [13]. Current guidelines in both the Netherlands and the United Kingdom (UK) for the management of RFM recommend ultrasound for fetal biometry assessment and quantification of amniotic fluid, as well as cardiotocography. Doppler measurements are not recommended in these guidelines other than in research setting [14, 15]. However, in 2017–2018 the CPR was already implemented in 22% of local protocols in the Netherlands and this percentage has probably increased since then [13].

The Lancet Stillbirth series identified the link between RFM and stillbirth as key priority for research [16]. It has been suggested to add other (bio) markers of placental dysfunction to biometry measurements in women reporting RFM [17]. Aside from the Doppler measurements mentioned before, the pulsatility index of the uterine artery is gaining attention as possible marker for placental function. A high uterine artery pulsatility index at term seems to be independently associated with an increased risk of adverse perinatal outcome regardless of fetal size [18]. Furthermore, maternal serum markers for placental function, such as serum soluble fms-like tyrosine kinase-1 (sFlt-1) and placental growth factor (PlGF), have considerable association with adverse outcomes [19, 20]. None of these studies performed subgroup analyses for women reporting RFM. The effect of a societal-awareness-intervention of women reporting RFM was assessed in a large trial including over 400,000 pregnant women. The intervention did not result in a significant reduction of stillbirths, yet did increase iatrogenic (relative preterm) births, suggesting that the solution may not be found in societal awareness but in a better risk assessment at the individual level [21].

The aim of this cluster randomised trial is to compare outcomes in women presenting with RFM at term, randomised to either expectant management or immediate induction of labour based on a low CPR for gestation. We will compare neonatal and maternal outcomes, as well as the healthcare costs in both groups. We will also evaluate the predictive value of serum biomarkers (sFlt-1 and PlGF).

## Methods

### Study objective

To assess whether expedited delivery (induction of delivery within 16 h) in pregnancies at term complicated with RFM and an abnormal CPR (< 1.1) improves neonatal outcome as compared to clinical management where the CPR remains concealed.

### Study design

We will conduct an international cluster randomised controlled clinical trial with randomisation at hospital level to either an open (CPR revealed) or concealed arm, performed in the Netherlands, UK and Australia. The protocol was drafted in accordance with the SPIRIT (Standard Protocol Items: Recommendations for Interventional Trials) statements [22]. The trial was registered at the Dutch Trial Registry (NTR 7557) prior to the start of inclusion, and is embedded within the Dutch Society of Obstetrics and Gynaecology’s (Nederlandse Vereniging van Obstetrie en Gynaecologie) NVOG clinical trial consortium, a collaboration of gynaecology and obstetric departments in the Netherlands.

### Randomisation

Participating hospitals will be randomised to either concealed or revealed CPR results for the duration of the study. Hospitals will be randomised using a computer-generated algorithm, stratified by country and number of deliveries per year.

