### Interventions

After recruitment and consent, an ultrasound scan for fetal biometry, amniotic fluid volume, uterine artery pulsatility index and CPR is performed. The pulsatility indices of both the umbilical artery and middle cerebral artery will be reported aside from the calculated CPR. Depending on the cluster, clinicians will be either blinded or unblinded to the CPR. Expedited delivery is pursued in women with an abnormal CPR – defined as an CPR < 1.1 - in the open arm. In this case we aim to start delivery within 16 h or an elective caesarean section will be advanced. There are no criteria for discontinuing the intervention other than participant request. In this case she will be followed-up for intention-to-treat analysis. Women in the concealed arm will not have their CPR results revealed and will receive routine clinical care (Fig. 1).

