**Fig. 1 Fig1:**
[figure not shown]
Flow chart of the CEPRA study design and interventions. ^a^ Blood sample will not be drawn from participants with a normal CPR in the open arm. ASQ: Ages and Stages Questionnaire, CBCL: Child Behaviour Checklist, CPR: cerebroplacental ratio, CTG: cardiotocograph, EQ-5D-5L: European Quality of life 5-Dimension 5-Level, PCL-5: posttraumatic stress disorder checklist for DSM-5, SGA: small for gestational age, WDEQ: Wijma Delivery Expectancy/Experience Questionnaire

A maternal blood sample will be taken from *all participants* in the *concealed arm* and from participants with an *abnormal CPR* in the *open arm* for serum biomarker analyses and will be stored locally. Analyses are performed in batch after study closure.

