## Statistical analysis

### Data analysis plan

The primary analysis will estimate the relative risk (RR) with 95% confidence intervals and *p*-values for the composite perinatal outcomes, using a generalized linear mixed model with log link and binomial distribution, with random intercepts and random slopes per cluster. The primary analysis will be performed according to the intention-to-treat principle. A per protocol analyses will be done as secondary analysis.

Dichotomous secondary outcomes will be analysed using the same method as the primary outcome. Continuous data of secondary outcomes will be assessed using a linear mixed model to estimate mean differences, with random intercepts and slopes as appropriate. Median differences will be calculated as appropriate. A significance level of 5% will be used for all tests. Interim testing for efficacy will not be performed, hence the significance level does not need to be lowered.

Given that all required data is collected for routine patient care in both primary and secondary care, missing data is expected to be limited. Multiple imputation will be used if required.

Data of quality of life measures will be obtained at four time points and will be analysed using generalised estimating equations.

For subgroup analyses we will assess the relationship between pregnancy characteristics, outcomes and abnormal serum biomarkers of PlGF and sFlt-1.

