## Ethics and disemmination

### Patient consent

Eligible patients obtain verbal and written information when the CTG appears normal. The information can be read during the CTG recording and a short animation video that has been developed to provide a study summary in laymen’s terms can be watched. If a patient agrees to participate, written informed consent will be obtained by an authorized person. Additional consent will be obtained to store the residual material of the maternal blood sample in a biobank for 50 years and to be approached for follow-up- and future research.

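### Women are recruited after their hospital's fixed arm can be known, and the stated primary model names no baseline factor, so differential recruitment can bias the relative risk

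*Protocol article*

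**What the plan says.** Allocation is by hospital and permanent: "Participating hospitals will be randomised to either concealed or revealed CPR results for the duration of the study". The stratifiers are hospital-level only: "Hospitals will be randomised using a computer-generated algorithm, stratified by country and number of deliveries per year".

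Recruitment is individual and comes later. The Patient consent section has information given around the cardiotocograph, and then "If a patient agrees to participate, written informed consent will be obtained by an authorized person". The study scan follows consent (Interventions).

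What is masked is the Doppler result, not the allocation: "Depending on the cluster, clinicians will be either blinded or unblinded to the CPR".

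The consequences of joining differ by arm:
- **Open arm:** "Expedited delivery is pursued in women with an abnormal CPR". For blood sampling, the Fig. 1 legend says "Blood sample will not be drawn from participants with a normal CPR in the open arm".
- **Concealed arm:** "Women in the concealed arm will not have their CPR results revealed and will receive routine clinical care". Blood is taken from every participant.

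The Data analysis plan estimates the primary relative risk "using a generalized linear mixed model with log link and binomial distribution, with random intercepts and random slopes per cluster". It names no baseline characteristic of the woman and neither stratifier.

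**The concern.** Randomising hospitals balances hospitals in expectation. It does not balance women who are enrolled once the arm is fixed. A concealed hospital must run a special procedure to withhold the result, and an open hospital must act on it, so staff who recruit can hardly be unaware of their arm. The Strengths and challenges section expects clinicians and women to be reluctant to wait once a low ratio is known, which shows that preferences here are strong. Staff could approach different women in the two arms, and different women could accept.

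Cluster random effects absorb variation between hospitals. They do not remove a systematic difference between arms in who enrols.

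At stake is the primary relative risk itself. The sample size section puts 11 of the 12 percentage points of the composite in a group that includes emergency delivery for fetal distress. If that component depends on factors such as parity or gestational age (an assumption, not stated in the article), a difference in mix would appear as an intervention effect or would hide one.

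**Working it through.** **Inputs from the protocol article (Sample size calculation).** Risks of 12% and 8% (relative risk 0.667), 24 clusters of 90, 1,080 women per arm, intra-cluster correlation 0.002, alpha 5% (taken as two-sided), stated power 80.06%.

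**Step 1: the plan's own figure.**
- Design effect = 1 + (90 − 1) × 0.002 = 1.178.
- Effective number per arm = 1,080 / 1.178 = 916.8.
- Standard error, pooled: √(2 × 0.10 × 0.90 / 916.8) = 0.01401. Unpooled: √((0.12 × 0.88 + 0.08 × 0.92) / 916.8) = 0.01398.
- Power = Φ((0.04 − 1.96 × 0.01401) / 0.01398) = Φ(0.897) = 81.5%.
- A continuity correction gives 79.4%, and a t test with 22 degrees of freedom gives 78.1%.

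The stated 80.06% is reproduced to within 2 points. The sample size is not in error, but it takes baseline risk to be equal in the two arms.

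**Step 2: assumed inputs.** None of these is in the article. Average risk without intervention is 12%. Half the women belong to a high-risk baseline group (for example, nulliparous). The risk ratio between groups is 2 (risks 8% and 16%) or 3 (6% and 18%). The open arm's share of high-risk women differs by 5 or 10 points.

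**Step 3: shift in baseline risk** = difference in share × difference in risk. For example, 0.10 × (0.16 − 0.08) = 0.8 points, and 0.10 × (0.18 − 0.06) = 1.2 points.

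**Step 4: type I error with no true effect.** Standard error = √(2 × 0.12 × 0.88 / 916.8) = 0.01518. With k = shift / 0.01518, type I error = Φ(−1.96 − k) + 1 − Φ(1.96 − k).

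**Step 5: power if the shift runs against the open arm.** The true relative risk is held at 0.667, so the open-arm risk = 0.667 × (12% + shift). It is compared with 12% by the Step 1 formula.

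| Difference in mix | Risk ratio | Shift (points) | k | Type I error | Open-arm risk | Apparent relative risk | Power |
|---|---|---|---|---|---|---|---|
| 5 points | 2 | 0.4 | 0.26 | 5.8% | 8.27% | 0.689 | 75% |
| 5 points | 3 | 0.6 | 0.40 | 6.8% | 8.40% | 0.700 | 72% |
| 10 points | 2 | 0.8 | 0.53 | 8.2% | 8.53% | 0.711 | 69% |
| 10 points | 3 | 1.2 | 0.79 | 12.4% | 8.80% | 0.733 | 61% |

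If the shift favours the open arm, a true 0.667 appears as 0.644 to 0.600 over the same four rows, and the benefit is exaggerated. These are two-proportion approximations with a design effect, not fits of the planned mixed model.

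**The case against.** The strongest reply is that covariates are commonly left to an analysis plan, which is not shown, and that this is a condensed article. The Data analysis plan gives link, distribution and random effects. It does not call the estimate unadjusted or rule out fixed effects. Nothing elsewhere in the article contradicts it. This stands as a limit: the point concerns the model as stated, and an unseen plan may already list covariates. It does not remove the point, because the exposure comes from the design in the article and the stated model would not address it.

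The cluster design is also deliberate and reasoned, and one eligibility list serves both arms. Both are true. However, a common list does not make approach and consent equal when the arm is known.

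A reader might infer more than the documents support:
- **That the woman certainly knows her arm before consenting.** No section says she is told, or that the consent material differs by arm. Even the recruiters' knowledge is an inference, though a strong one.
- **That the relative risk will be biased.** The article shows exposure only. Nothing in it shows, for instance, that blood sampling affects consent.
- **That chance differences in case mix between hospitals add to the bias.** They are sampling variation, which the intra-cluster correlation and the random effects are there to cover.
- **That power could fall to about half.** That requires adding the full control-risk shift to the open arm's 8%. The plan's effect measure is a relative risk, and with a constant relative risk the lowest figure in this illustration is 61%.

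**Conclusion.** The concern holds as an exposure to recruitment bias that the stated primary model does not correct. Allocation is fixed by hospital, consent comes afterwards, and the consequences of joining differ by arm. Neither the size nor the direction of any bias can be derived from the documents. The figures in the table depend wholly on the assumed 50% prevalence, the risk ratio of 2 to 3 and the 5- or 10-point difference in mix. On those inputs the effect runs from slight (type I error 5.8%, power 75%) to material (12.4%, 61%). The sponsor should make the change, but the point does not invalidate the design or the sample size.

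**What to change.** In the Data analysis plan, make the primary relative risk adjusted for a short pre-specified list of factors fixed before the cerebroplacental ratio is known: parity, gestational age at presentation, estimated fetal weight centile and previous caesarean. Add the two randomisation stratifiers, country and annual number of deliveries. If the log-binomial mixed model does not converge, obtain the relative risk by marginal standardisation from a logistic mixed model. Keep the unadjusted estimate as a sensitivity analysis.

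Report baseline characteristics by arm and, where sites can log them, the numbers approached and consenting by arm, so that readers can judge whether recruitment differed.

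The cost is mainly analysis wording. The covariates come from the obstetric history and the study scan, and no extra patients are needed. The downsides are small: the convergence fallback may be needed, sites that can do so keep a log, and adjustment removes only imbalance in factors that were measured.

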### Sample size calculation

We estimate a reduction of the incidence of the composite adverse neonatal outcome from 12 to 8%. The background risk of 12% is extrapolated from the existing literature on RFM as applicable to our population [2, 21, 25–29]. This is an extrapolation because there has been heterogeneity in reported outcome measures in RFM studies. We anticipate an incidence of stillbirth and neonatal mortality (< 28 days) of 0.5%, and an incidence of Apgar score < 7 at 5 min and/or pH < 7.10 umbilical artery and/or emergency delivery for fetal distress of 11% (indicative for peripartum asphyxia). The less common events are grouped into severe neonatal morbidity and include: need for cooling, respiratory distress syndrome, hypoxic ischemic encephalopathy, sepsis, necrotizing enterocolitis and, supplementary oxygen therapy (> 4 days). For severe neonatal morbidity we anticipate an incidence of 1% of which 0.5% overlaps with peripartum asphyxia.

Based on these assumptions, a total of 2160 patients obtained from 24 clusters with 90 patients per cluster (equal numbers of control and intervention), achieve 80.06% power to detect a difference in the primary outcome from 12 to 8%, with an alpha of 5%, and an intra-cluster correlation of 0.002.

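### The primary model names no term for the country and delivery-volume strata used in randomisation; if these strata are prognostic, standard errors are somewhat too large and a little power is forgone

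*Protocol article*

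**What the plan says.** The Randomisation section allocates hospitals with a computer-generated algorithm, "stratified by country and number of deliveries per year". Country has three levels, since the trial is "performed in the Netherlands, UK and Australia". The number of volume categories is not given.

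The Data analysis plan section states: "The primary analysis will estimate the relative risk (RR) with 95% confidence intervals" and p-values, "using a generalized linear mixed model with log link and binomial distribution, with random intercepts and random slopes per cluster". No fixed effect for country or delivery volume is named, and the text does not say that they are left out. Dichotomous secondary outcomes follow the same method, and continuous ones use a linear mixed model.

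The Sample size calculation section plans for "a total of 2160 patients obtained from 24 clusters with 90 patients per cluster" ("equal numbers of control and intervention"), which "achieve 80.06% power to detect a difference in the primary outcome from 12 to 8" per cent at an alpha of 5% and an ICC of 0.002. It claims no gain from stratification or adjustment.

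**The concern.** Stratified allocation balances the arms on the strata, so differences between strata no longer contribute to chance variation in the arm comparison. A model without the strata does not know this. It counts those differences as between-hospital noise and reports a standard error larger than the real one. The usual remedy is to carry the randomisation strata into the analysis.

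The model is specified down to link, distribution and random slopes, so an analyst following the text as written would fit it without the strata. Whether that matters depends on whether the strata predict the outcome. This is plausible: emergency caesarean and instrumental delivery fall in the component group expected to occur in 11% of women, against 12% for the whole composite, and such practice may differ between health systems. At stake are interval width and power in a trial planned at 80.06% power.

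**Working it through.** **Inputs.** From the Sample size calculation: 12% versus 8%, 24 clusters of 90, so 12 clusters and 1080 women per arm, ICC 0.002, alpha 5% (two-sided assumed). Not in the document, so varied: R², the share of between-hospital variance that the strata explain, from 0 to 1.

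**1. Planned power.**
- Design effect = 1 + (90 − 1) × 0.002 = 1.178.
- Effective number per arm = 1080 / 1.178 = 916.8.
- Two-proportion power, normal reference = 81.5%, within 2 points of the stated 80.06%.
- With a t reference on 24 − 2 = 22 degrees of freedom: 78.1%.

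**2. Bound by formula.** Adjustment replaces the ICC by 0.002 × (1 − R²).

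| R² | Design effect | SE relative to unadjusted | Power, normal | Power, t on 19 df |
|---|---|---|---|---|
| 0 | 1.178 | 1.000 | 81.5% | 77.5% |
| 0.25 | 1.134 | 0.981 | 83.0% | 79.0% |
| 0.5 | 1.089 | 0.962 | 84.4% | 80.6% |
| 1 | 1.000 | 0.921 | 87.3% | 83.8% |

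The 19 df assume three stratum parameters (two for country, one for two volume groups). The ceiling is 87.3 − 81.5 = 5.8 points, and the unadjusted SE is at most 1/0.921 = 1.085 times the adjusted one.

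**3. Why the realistic gain is below that ceiling.** Step 2 uses an unstratified design as its starting point. Under stratified allocation the estimate is already more precise, and only the reported SE is too large. At R² = 1:
- True SE = √[(0.12 × 0.88 + 0.08 × 0.92) / 1080] = 0.01288, so the expected z is 0.04 / 0.01288 = 3.105.
- The unadjusted test in effect demands 1.96 × 1.085 = 2.127, giving power Φ(3.105 − 2.127) = 83.6%.
- The adjusted test gives Φ(3.105 − 1.96) = 87.4%.
- The gain is 3.8 points, and the unadjusted type I error is 2 × [1 − Φ(2.127)] = 3.3%.

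**4. Simulation.** Cluster-level regression with a t reference, 3 countries × 2 volume groups (assumed), 4 hospitals per stratum, 6000 runs per scenario, total ICC 0.002:

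| R² | Power, unadjusted | Power, adjusted | Type I error, unadjusted |
|---|---|---|---|
| 0 | 77.4% | 76.6% | 4.8% |
| 0.5 | 79.2% | 80.3% | 4.6% |
| 1 | 82.1% | 84.6% | 4.1% |

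Stratum effects were redrawn in each run. Three country draws realise on average 2/3 of their nominal variance and two volume draws 1/2, so the realised share is about 0.5 × 2/3 + 0.5 × 1/2 = 0.58. The simulated gain at R² = 1 is therefore on the low side of step 3; both lie under the ceiling of step 2.

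A separate simulation fixed the country risks (12/10.6/13.4%), with country explaining about half of a total ICC of 0.002. It gives type I error 4.1% unadjusted versus 5.0% adjusted, and power 79.2% versus 80.9%.

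**5. If the ICC is higher (assumption: 0.01).** Unadjusted versus adjusted power is 63.0% versus 68.9% at R² = 0.5 and 70.2% versus 83.5% at R² = 1. Unadjusted type I error is 3.9% and 2.4%.

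**6. Cost if the strata are not prognostic.** By formula 78.1 − 77.5 = 0.6 points; in simulation 77.4 − 76.6 = 0.8 points.

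**The case against.** The strongest objection is that this is silence in a condensed article: it lists no covariates, does not exclude the strata, and an analysis plan that is not shown may include them. That stands as a caution. A reader might infer that the sponsor has decided to ignore the strata; the text does not support this. But the article gives the model in detail, and that model does not match the stratified design. If the analysis plan already has the terms, confirming so closes the point.

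A second objection is that nothing shows the strata to be prognostic. The Background's remark on variation between countries concerns stillbirth, and stillbirth plus neonatal death is expected in only 0.5% of women. The practice variation described in the Background and Discussion concerns use of the cerebroplacental ratio and Doppler, not delivery rates. This stands, so the loss must be stated conditionally.

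A third objection is that the sample size already uses the full ICC, so omitting the strata forgoes a bonus and does not take power below plan. This also stands.

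A stronger reading is tempting: that power falls to 70% or even 61%. Simulations do give such figures (70% unadjusted versus 76% adjusted, and 61% versus 75%) with 12, 6 and 6 hospitals per country and control risks of 10/12/14% or 9/12/15%. But these place country variance on top of an ICC of 0.002:
- For 10/12/14% the mean risk is (12 × 10 + 6 × 12 + 6 × 14)/24 = 11.5%. The between-country variance is 0.000275, which adds 0.000275/(0.115 × 0.885) = 0.0027, for a total ICC of about 0.005.
- For 9/12/15% the mean is 11.25% and the added ICC about 0.0062, for a total of about 0.008.

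The document gives 0.002 simply as the intra-cluster correlation, and its control risk is 12%. Those figures describe a different, assumed trial.

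**Conclusion.** The point holds in conditional form. The stated primary model does not carry the randomisation strata. If country or volume predicts the composite outcome, its standard errors are somewhat too large (at most about 8.5% at the planned ICC), its test falls below 5%, and it forgoes some power. At a total ICC of 0.002 the simulated gain from adjustment runs from nothing to about 2.5 points, with a formula ceiling of about 6. It is larger only if the true ICC across the three countries is above 0.002. There is no bias and no type I inflation.

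This rests on two-sided alpha, equal cluster sizes, few volume categories and an R² that the document does not give. A reader might extend the point to patient covariates such as parity, gestational age or previous caesarean. Neither the stratification statement nor any calculation here supports that, so such covariates remain optional.

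**What to change.** In the Data analysis plan, state that the primary model includes fixed effects for country and for a coarse delivery-volume category, and apply the same to the secondary mixed models. Keep the volume categories few, because there are only 24 clusters. Settle this before unblinded outcome data are seen. If the analysis plan already contains these terms, align the wording.

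The cost is a change of text with no new data. It uses about three between-hospital degrees of freedom (22 to 19 with two volume groups), which is under 1 point of power if the strata prove not to be prognostic.
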